### Randomization

Older adults who meet the inclusion criteria in the geriatric department will be numbered according to the time of admission. Moreover, we will use R and adopt a block randomization method to randomly assign patients to the control and intervention groups in a 1:1 ratio. This study will be open-label.

### Measurements

#### Assessment

The initial assessment will be completed within 48 h of admission. Subsequently, follow-up by telephone will be performed at 3, 6, and 24 months after discharge. Additionally, a face-to-face follow-up will be conducted at 12 months after discharge (Fig. 2). SPPB will be used to assess mobility. SPPB is a well-established tool for assessing lower extremity physical performance status. It includes balance, pace, and standing-sitting tests, with a total score of 0–12, with lower scores indicating poorer exercise capacity [38]. The activities of daily living (ADL) and the functional impairment screening tool (FIST) scales will be used to assess physical function. The FIST assessment entails 16 questions with a total score of 16. The higher the score, the better the performance [39]. We will use Geriatric Depression Scale (GDS) -15 to assess depression. It has a total score of 15 points, with 5–9 indicating that the patient may be prone to depression and ≥ 10 indicating depression [40, 41]. The Short Form-12 will be used to assess the quality of life [42]. Fried frailty phenotype includes unintentional weight loss, exhaustion, weakness, slowness, and low physical activity. A score of 0 indicates robustness, 1–2 indicates pre-frail, and ≥ 3 indicates frailty [43]. Moreover, we will evaluate social frailty using the Help, Participation, Loneliness, Financial, and Talk (HALFT) scale, and those who score ≥ 3 will be classified as socially frailty, 1–2 as pre-social frailty, and 0 will be considered normal [44]. Additionally, the Morse Fall Risk Scale will be used to assess falls. Scores ≤ 23, 24–44, and ≥ 45 are classified as low intermediate and high risks, respectively [45].

**Fig. 2 Fig2:**
[figure not shown]
Schedule of enrollment, measurement, allocation, intervention, and follow-up. SPPB, Short-Physical Performance Battery; ADL, Activities of daily living; GDS-15, Geriatric Depression Scale; SF-12, The Short Form-12; MMSE, Mini-Mental State Examination; MNA-SF, Mini Nutritional Assessment short-form; IC, Intrinsic Capacity

Furthermore, we will assess sarcopenia using SARC-CalF, which includes six questions: lifting 10 pounds, walking from one end of the room to the other, moving from a chair to a bed, climbing one flight (10 steps) of stairs, number of falls in the past 1 year, and calf circumference. Patients with a score ≥ 11 will be considered to have a high risk of sarcopenia [46, 47]. MMSE will be used to assess cognition. Its scores range from 0 to 30, with 21–26, 10–20, and 0–9 indicating mild, moderate, and severe cognitive impairments, respectively [48, 49]. Nutritional status will be assessed using the Mini Nutritional Assessment Short-Form (MNA-SF) [50–52]. A score of 0–7 means the patient is malnourished, 8–11 means risk of malnutrition, and 12–14 indicates normal nutritional status. Intrinsic capacity includes five aspects: cognitive decline, limited mobility, malnutrition, sensory loss, and depressive symptoms [53].

#### Bone mineral density

We will use an X-ray osteodensitometer (LUNAR iDXA, GE Healthcare, Madison, WI, USA) to measure bone mineral density, T-score, and Z-score of the lumbar spine and femoral bone in older adults.

#### Body composition

We will use a body composition meter (JAWON-IOI353, Jawon Medical, Gyeongsan, Korea) to measure the body fat mass, soft lean mass, and basal metabolic rate of older adults through bioelectrical impedance analysis.

#### Laboratory data

We will measure the following parameters: leukocyte counts, hemoglobin concentration, blood biochemistry, coagulation, glycated hemoglobin, brain natriuretic peptide, C-reactive protein, interleukin-6, vitamin D, and ferritin.

### Intervention scheme

Patients with mobility limitation will be randomly divided into control (routine standard clinical procedures) and intervention groups (MDT + routine standard clinical procedures) (Fig. 3).

**Fig. 3 Fig3:**
[figure not shown]
Multidisciplinary team (MDT) intervention program. MDT is based on routine medical procedures with exercise intervention as the core. The multidisciplinary consultation team includes ophthalmologists, otolaryngologists, neurologists, cardiologists, rheumatologists and immunologists, endocrinologists, psychologists, and pain management physicians

#### Exercise intervention

The exercise intervention plan will be based on the ICFSR (2021) recommendation [54], using the M-MobiLE exercise program and adjusting the exercise program and frequency guided by a rehabilitation physician. The M-Mobile exercise intervention plan includes aerobic, resistance, balance, and stretching exercises (Fig. 4).

**Fig. 4 Fig4:**
[figure not shown]
The M-MobiLE exercise intervention program includes aerobic, resistance, balance, and stretching exercises. An individualized exercise program will be developed for the patient based on SPPB scores

Aerobic exercises will be conducted for 30–60 min daily, and the exercise duration can be gradually increased. Patients will be asked to complete at least 150 min of aerobic exercise per week, at least 5 days a week, at an intensity such that the patient has mild dyspnea when active but can still talk easily. Resistance exercises will be performed progressively, gradually increasing the amount of exercise. Patients will perform muscle-strengthening activities at least two days a week. Balance exercise will be based on the actual situation of older adults to choose a suitable method and prevent injury. Patients can borrow a stable chair for assistance at the beginning of the exercise or exercise accompanied by others. Stretching exercises will be performed at least twice a week. The specific amount of exercise will be determined during the training by a rehabilitation physician to ensure exercise safety. During hospitalization, patients in the intervention group will be trained 3–5 times weekly. After the exercise, patients will record their experienceit in the exercise manual: easy, difficult, or very difficult. Additionally, patients will be instructed to keep recording in their exercise diaries after discharge, filling in the number of completed weekly sessions and training experience until the last follow-up.

#### Educational interventions

The nursing team will distribute mobility limitation treatment brochures to patients and instruct patients who can get out of bed to avoid prolonged bed rest during hospitalization.

#### Nutritional interventions

Nutritional interventions will be determined based on the MNA-SF scores and nutritionist's recommendations.

#### Pharmacological interventions

If a medication significantly increases the risk of mobility limitation, the pharmacist will help geriatrician consider whether to discontinue, switch, or reduce the dose.

#### Comorbidity management

Geriatricians will cooperate with other multidisciplinary consultation teams to diagnose and intervene in the risk factors associated with mobility limitation. The multidisciplinary consultation team will include ophthalmologists, otolaryngologists, neurologists, cardiologists, rheumatologists and immunologists, endocrinologists, and pain management physicians. Additionally, patients with psychological diseases will be transferred to the psychology department for further treatment.

#### Environmental interventions

Geriatricians, rehabilitation physicians, and nursing teams will educate patients and their families on reasonably optimizing the home environment to avoid adverse events, such as falls.

### Study outcomes

The core of this study is to explore the effect of MDT on mobility in older adults with mobility limitation. The primary outcome is a change in the SPPB score, and secondary outcomes include changes in ADL, FIST, GDS-15, SARC-CalF, MMSE, MNA-SF, and intrinsic capacity scores.

### Sample size

This will be a parallel randomized-controlled study, and the ratio of the intervention to the control group will be 1:1. A randomized-controlled trial (RCT) in 2021 [55] reported an SPPB of 6.1 points in the control group, and the mean difference between both groups after exercise intervention was 2.4 [56]. Our sample estimate is a one-sided test with a first-class error of 0.025 and a power of 90%. The sample size N1 = N2 = 26 was calculated using PASS 15. Assuming that the rate of loss to follow-up is 20%, the minimum sample size will be N1 = N2 = 26/0.8 = 33. Therefore, a minimum of 66 patients will be recruited for this study.

### Data collection, validation, and management

The medical data will be collected using the Hospital Information System. Additionally, data input will be done by trained staff using Epidata. The database will be checked by the data administrator, who will desensitize, structure, standardize, and control the data, design the corresponding database system project according to the research plan, and set logical check conditions for entry.

### Statistical analysis

Baseline characteristics will be described using statistics, such as mean ± SD, mean rank, or number and percentage. Differences in the characteristics between both groups of outcomes will be assessed using chi-square/Fisher’s exact test for categorical variables and t-test/Wilcoxon-rank sum test for continuous variables. Potential confounding factors will be analyzed using univariate and multivariate logistic regression analyses. The statistical significance will be set at *p* < 0.05 (two-tailed), and statistical analyses will be performed using R.

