## Method and design

### Study design and setting

We will conduct a prospective, multicenter, randomized, parallel, and controlled trial in the geriatric departments of at least five hospitals. A two-arm follow-up cohort will be established in this study. The control group will be placed on routine treatments, and the intervention group will be treated with an MDT approach, including exercise, educational, nutritional, medical, comorbidity, and environmental interventions. The multidisciplinary consultation team will include geriatricians, rehabilitation physicians, nutritionists, nurses, pharmacists, ophthalmologists, otolaryngologists, neurologists, cardiologist, rheumatologists, endocrinologists, psychologists, and pain management physicians. Furthermore, we will develop an individualized exercise prescription based on the “International Exercise Recommendations in Adults (ICFSR): Expert consensus guidelines” and the recommendations of the rehabilitation physician. The assessment for mobility limitation will be completed within 48h after admission, followed by MDT. Guidance recommendations for comprehensive interventions will be extended to 2 years after discharge, and follow-up assessments will be performed at 3, 6, 12, and 24 months after discharge (Fig. 1).

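### The two-sample tests named for continuous outcomes use one visit at a time and have no hospital term, which loses precision for secondary scores assessed at several follow-ups

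*Protocol article*

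**What the plan says.** The Statistical analysis section of the protocol article assesses group differences with chi-square or Fisher's "exact test for categorical variables and t-test/Wilcoxon-rank sum test for continuous variables". The only other method it names is a regression for confounders: "Potential confounding factors will be analyzed using univariate and multivariate logistic regression analyses". That model is logistic, so it describes neither a continuous score nor repeated visits.

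The design has two features that these tests do not use. Study design and setting places the trial in the "geriatric departments of at least five hospitals", and "follow-up assessments will be performed at 3, 6, 12, and 24 months after discharge". The Assessment section adds that "follow-up by telephone will be performed at 3, 6, and 24 months after discharge", with month 12 face to face.

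On allocation, the Randomization section says "Older adults who meet the inclusion criteria in the geriatric department will be numbered according to the time of admission", and that the trial will "adopt a block randomization method to randomly assign patients to the control and intervention groups in a 1:1 ratio". It does not say whether the blocks run within each hospital.

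Study outcomes makes change in SPPB primary. It lists seven secondary scores: ADL, FIST, GDS-15, SARC-CalF, MMSE, MNA-SF and intrinsic capacity.

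**The concern.** A t-test or Wilcoxon test on a score collected several times gives one separate comparison per visit, up to four per score, with no stated way of combining them. It ignores the correlation between a patient's visits. A patient who misses one contact leaves that comparison even if the other contacts were completed. With 26 evaluable patients per arm planned and 20% loss expected, that information is worth keeping.

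The second feature is hospital. The control treatment is each hospital's routine care, so outcomes may differ between hospitals. A pooled two-sample test leaves any such difference in the error term. Whether this miscalibrates the test, or only affects its efficiency, depends on how the blocks were formed.

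What is at stake is precision. Nothing here raises the risk of a false positive.

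**Working it through.** **The plan's own figure.** Sample size gives a difference of 2.4 SPPB points, one-sided 0.025, 90% power and 26 per arm. It states no SD, so the 26 cannot be reproduced from the text alone. Solving backwards gives an SD of 2.62 to 2.67 (normal formula) or 2.57 to 2.62 (t-based). The dropout step reproduces: 26/0.8 = 32.5, so 33 per arm and 66 in total. An SD of about 2.6 and 52 evaluable patients are assumed where needed below.

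**Repeated visits.** Take a score measured at all four follow-ups, with equal variances and a common correlation ρ between visits (compound symmetry). Relative to a single visit, the variance of the visit-averaged arm difference is (1 + 3ρ)/4. The correlation is an assumption; the article gives none.

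| ρ | (1 + 3ρ)/4 | Equivalent gain in patients |
|---|---|---|
| 0.5 | 0.625 | 1/0.625 = 1.60, or 60% |
| 0.6 | 0.700 | 1/0.700 = 1.43, or 43% |
| 0.7 | 0.775 | 1/0.775 = 1.29, or 29% |

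Scores taken at two or three visits gain less. Fig. 2, which shows what is measured when, is not available here, so the number of visits per score cannot be settled.

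**Does this reach SPPB?** The Assessment section describes SPPB as balance, pace and standing-sitting tests. These cannot ordinarily be done by telephone, and three of the four contacts are by telephone. Month 12 may be the only post-discharge SPPB, so no gain from repeated visits is shown for it.

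**Hospital, blocks within hospital.** Take five hospitals of similar size and let the ICC (assumed) be the share of variance between hospitals. With a total variance of 1, the pooled error variance is about (1 − ICC) + ICC × (4/5) × 52/50. With a hospital term it is 1 − ICC.

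- ICC 0.10: 0.900 + 0.083 = 0.983. √(0.983/0.900) = 1.045.
- ICC 0.20: 0.800 + 0.166 = 0.966. √(0.966/0.800) = 1.099.

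Simulation (blocks of four, 52 or 66 patients) puts the average excess in the standard error slightly lower, at about 4% and 9%. The pooled t-test's two-sided error is about 3.9% to 4.6% at ICC 0.10 and between 3% and 4% at ICC 0.20. A hospital term adds about 1.1 and 2.5 points of power respectively. If hospitals do not differ and the arms are balanced within them, the term costs about 0.1 point (90.0% with 50 df, 89.9% with 46 df).

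**Hospital, one list with admissions from the hospitals interleaved.** The simulated two-sided error is about 4.6% to 5.6% for ICCs of 0.05 to 0.20, which is nominal within simulation error. Arms are then unbalanced by chance within hospitals. A hospital term costs about 2 to 3 points of power at ICC 0, makes little difference at 0.10, and gains about 2 to 3 points at 0.20.

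**The case against.** The strongest reply is that the section is a few sentences in a journal article, and that model terms and covariance structures belong in an analysis plan not shown here. That is right for the details. But the article does not leave the test open. It names two-sample tests, and any fuller plan would have to agree with that text or replace it.

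A reader might infer that the trial's confidence interval is too wide and its true error rate below 5%. The document does not support that as a general statement. It holds only if blocks are balanced within hospital, which Randomization does not state. Numbering patients by admission time can be read as one list per department or as one list for the trial, and under the second reading with mixed-order admissions the pooled test is valid.

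A reader might also infer that repeated SPPB data go unused. The telephone contacts make that doubtful, and the text cannot settle it.

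Two further objections stand in part. The hospital effect is small, its ICC is assumed, and change from baseline may already remove stable differences in level between hospitals. The visit-averaged contrast is also a different estimand from the effect at one visit, so it should be reported alongside the visit-specific differences. Neither answers the loss from analysing repeated secondary scores one visit at a time.

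**Conclusion.** The point holds as a matter of precision, mainly for the secondary scores. For any score taken at more than one follow-up, the named tests discard information and lose patients visit by visit. With four visits, compound symmetry and ρ of 0.5 to 0.7, the visit-averaged variance is about 62% to 78% of the single-visit variance.

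The hospital part is smaller and conditional. With blocks within hospital and an ICC of 0.10 to 0.20, the pooled test is mildly conservative: two-sided error about 3% to 4.6%, standard error 4% to 9% too large. With one mixed-order list it is valid, and a hospital term may gain or lose a little power.

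The validity of the primary comparison is not threatened, and no repeated-visit loss is shown for SPPB.

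**What to change.** In Statistical analysis:

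1. For each secondary score measured at more than one follow-up, use a mixed model for repeated measures with arm, visit, arm-by-visit and baseline value. Report the arm difference with its 95% CI at each visit and averaged over visits. Keep the t-test/Wilcoxon comparison as a sensitivity analysis. A patient with a missed contact then contributes the visits that were completed, on the assumption that missingness is at random given the observed data.
2. State in Randomization whether blocks run within hospital. If they do, include hospital in this model and in the SPPB model, with a stated rule for merging very small sites.

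The Exclusion criteria section counts a patient who misses any follow-up as lost to follow-up. The wording should make clear that visits already collected from such a patient still enter the model.

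The cost is a revised paragraph, some programming in R and a few degrees of freedom (four for five hospitals). No new data are needed: visits are scheduled and each patient's hospital is known.

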## Discussion

As a geriatric syndrome with an extremely high prevalence, the diagnosis, evaluation, and treatment of mobility limitation are critical. Besides influencing various diseases, such as heart disease, respiratory disease, depression, and cognitive impairment [11, 23–25], mobility limitation increases the risk of falls, fractures, and death [14, 15]. As research on mobility limitation increases, so has the discovery of its influencing factors. These risk factors, including obesity, malnutrition, and low physical activity, can be intervened to prevent, alleviate, and treat mobility limitation [16–20]. Therefore, the complex factors that influence mobility limitation should be identified, and a comprehensive and individualized MDT program to reduce its prevalence should be formulated.

Many patients with mobility limitation have other comorbid diseases or functional impairments, and these factors are often mutually causal with mobility limitation [1]. Furthermore, although treating mobility limitation from a single angle may be effective, this approach is not comprehensive, limiting the treatment effect. Similar to the barrel effect, it may manifest as a mobility limitation if comorbidity is not addressed. Therefore, effectively managing or alleviating mobility limitation presents a challenge for geriatric doctors and nurses.

Comprehensive geriatric assessment can identify the risk factors associated with mobility limitation and reveal functional impairment in patients with mobility limitation [57, 58]. Based on this assessment, individualized routine exercise and educational, nutritional, medical, and comorbidity interventions can comprehensively eliminate or alleviate the causes of mobility limitation and treat or prevent complications. Therefore, MDT may be an important approach to effectively treat mobility limitation, and it is crucial to initiate treatment of mobility limitation in a hospital setting.

Many studies have assessed univariate interventions for treating patients with mobility limitation in the community or hospitals, identifying positive effects, such as reduced fall rates and mortality. However, no research has examined the effects of the MDT approach in treating mobility limitation using RCTs in the hospital setting. Therefore, this study aims to evaluate the effectiveness of MDT in patients with mobility limitation in a hospital setting. This study will provide novel ideas for treating mobility limitation, consequently reducing adverse prognosis, shortening the length of hospital stay, decreasing hospitalization costs, and improving the quality of life of older adults.

## Data Availability

The data will be used under license for the current study, and further inquiries can be directed to the corresponding author/s.

## Abbreviations

ADL: Activities of Daily Living
FIST: Function Impairment Screening Tool
GDS-15: Geriatric Depression Scale
MDT: Multidisciplinary Team
MMSE: Mini-Mental State Examination
MNA-SF: Mini Nutritional Assessment short-form
RCT: Randomized Controlled Trial
SF-12: Short Form − 12
SPPB: Short-Physical Performance Battery
